### Interventions

2.6

Eligible participants will be provided with standardized health education concerning the management of pulmonary nodules. This education encompasses advice on fostering a positive mindset, adhering to a balanced diet, ceasing smoking, limiting alcohol consumption, engaging in regular physical activity, and minimizing exposure to smoke, dust, and irritant gases. Additionally, to maintain the integrity of oral and fecal microbiome and metabolomics analyses, participants will be advised to abstain from consuming probiotics (including yogurt, etc.) for one week prior to enrollment and throughout the duration of the interventional treatment period.

Intervention Group: Participants will be administered CJG orally. CJG is formulated from a compound herbal medicine preparation comprising *V. segetalis*, *P. grandiflorus*, *A. bidentata*, *C. aurantium*, *T. kirilowii*, *C. longa*, and *Pumex*, with the specific dosages being proprietary. Initially, active constituents are extracted from these medicinal sources. Subsequently, the extract is concentrated into a viscous paste, which is then combined with appropriate excipients such as starch and dextrin, and dried to yield uniform, easily dissolvable dry granules. These herbs are processed into 6 grams of non-decoction granules (one packet) by Sichuan Neo-Green Pharmaceutical Technology Development Co., Ltd. (Sichuan, China), in compliance with the Production Quality Management Code. Patients are advised to consume a total daily dose of 18 grams, divided into three 6-gram doses to be taken after each meal. Each dose should be dissolved in 100 mL of boiling water, stirred, covered, and allowed to cool to a temperature of 30–37° C before consumption. Throughout the three-month intervention period, the dosage administered to all participants remains constant, irrespective of age, as this formulation constitutes a standardized fixed dose for adults. Previous studies have confirmed the safety and efficacy of this dosage regimen (14). Quality control assessments conducted by the manufacturer verify adherence to the standards specified in the *Chinese Pharmacopoeia (2020 Edition)* (15).

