Control Group: Participants in the control group will be administered a matched placebo. This placebo, produced by the same manufacturer, is composed primarily of maltodextrin and food-grade coloring agents. It is designed to be indistinguishable from the CJG in terms of appearance (color and shape), odor, and packaging. The instructions for administration are identical to those provided to the intervention group.

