#### Exploratory outcomes

2.7.4

To explore the potential mechanisms by which CJG may treat pGGNs, a longitudinal biospecimen collection protocol has been established. Paired saliva and feces samples will be collected at baseline, mid-term (months 1 and 2), and end (month 3) of CJG treatment. For saliva, participants will fast for 2 h, rinsed their mouths, and collected 2–3 mL of unstimulated saliva by drooling into a sterile tube, which will then be frozen on dry ice and stored at −80° C. For feces, participants will collect approximately 5 g at home using sterile tools, avoiding air exposure and toilet water. These samples will be initially kept at −20° C and later transferred on ice to a central lab for storage at −80° C.

After assessing sample quality, total genomic DNA from microbial communities will be extracted. The V3-V4 regions of 16S rRNA will be amplified for high-throughput sequencing. Sequences will be preprocessed through filtering, denoising, and chimera removal, resulting in amplicon sequence variants (ASVs) for bioinformatic investigations. This will include *α*-diversity analysis with Shannon and Chao1 indices, *β*-diversity exploration using principal coordinate analysis (PCoA) with Bray-Curtis distance, genus-level species differentiation via Linear discriminant analysis Effect Size (LEfSe), and examining the relationship between microbial genus abundance and time using multivariate linear association (MaAsLin).

Metabolites were extracted from saliva and feces using a chilled methanol–water solution. After centrifugation, the supernatant was analyzed by LC–MS. The raw data were processed for peak alignment, de-noising, and normalization. Multivariate statistical analyses, such as principal component analysis (PCA), partial least squares discriminant analysis (PLS-DA) and orthogonal PLS-DA (OPLS-DA), identified differential metabolites (VIP > 1 and *p* < 0.05). Kyoto encyclopedia of genes and genomes (KEGG) enrichment analysis revealed altered pathways. The Benjamini-Hochberg method was used to calculate the false-discovery rate (FDR) for multiple comparisons, with significance set at *P*_FDR_ < 0.05.

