The direct cellular impacts of the human microbiota and microbial metabolites have the potential to reprogram the pulmonary microenvironment, thereby facilitating early-stage lung cancer. Current research suggests that the lung microbiome *Faecalibacterium* and *Blauti*a may exert protective effects against the progression of early lung cancer from ground-glass nodules to solid nodules, whereas *Ralstonia* may contribute to malignant transformation (30). The metabolites of these microbes are primarily involved in energy metabolism pathways. Additionally, the microbiota plays a crucial role in the translation of TCM. TCM extracts, monomers, and compound formulations can exhibit antitumor effects by modulating the composition of the gut microbiota and endogenous metabolites, restoring the integrity of the intestinal barrier, and regulating immune and metabolic processes (31). Our team developed a lung nodule risk prediction system using 16S rRNA sequencing and machine learning, which identified distinct salivary microbiota profiles between persistent nodules and healthy controls, as well as between benign and malignant nodules (32, 33). Besides, our up-front clinical trial on gut microbiota during CJG intervention for ground-glass nodules in the lung showed that this formulation altered gut microbiota, notably increasing *Weissella* abundance, which may influence clinical outcomes (34). However, this study specifically includes ground-glass nodules patients combined with constipation. And the small sample size, short duration, and unstable microbial findings limited deeper exploration of the interactions between CJG, gut microbiota, and ground-glass nodules. Thus, we hypothesize that CJG may affect pGGNs by altering the oral and gut microbiota’s composition and metabolic pathways. Our integrated multi-omics approach (16S rRNA sequencing and GC–MS metabolomics) serves as a powerful *in vivo* “wet lab” experiment conducted directly on patient-derived biospecimens. By analyzing the salivary and gut microbiota alongside their metabolic profiles, we aim to move beyond correlation and infer potential causal biological pathways through which CJG may exert its effects. Subsequent KEGG pathway enrichment analysis of identified differential metabolites will specifically highlight altered host or microbial metabolic pathways (e.g., involving inflammation, oxidative stress, or cellular proliferation), effectively bridging the gap between CT imaging findings and underlying molecular mechanisms. This bioinformatic exploration provides a robust hypothesis-generating framework for future targeted *in vitro* or *in vivo* mechanistic studies on specific signaling pathways.

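### The exploratory metabolomics samples participants on treatment and states no step to set aside product-derived compounds, so differential features cannot be attributed to host or microbial metabolism as written

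*Protocol article*

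**What the plan says.** **Sampling (2.7.4).** "Paired saliva and feces samples will be collected at baseline, mid-term (months 1 and 2), and end (month 3) of CJG treatment". No sample after the end of dosing is named. The preparation described before giving saliva is brief: "participants will fast for 2 h, rinsed their mouths, and collected 2–3 mL of unstimulated saliva". For stool, participants collect about 5 g at home; the handling rules concern sterility, air and toilet water, not the time of the last dose.

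**Products (2.6).** In the CJG arm, "Patients are advised to consume a total daily dose of 18 grams, divided into three 6-gram doses to be taken after each meal". The herbal extract is "combined with appropriate excipients such as starch and dextrin". The placebo "is composed primarily of maltodextrin and food-grade coloring agents", and "The instructions for administration are identical to those provided to the intervention group".

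**Analysis (2.7.4).** Peaks are aligned, de-noised and normalised. PCA, PLS-DA and OPLS-DA follow, and these "identified differential metabolites (VIP > 1 and *p* < 0.05"). KEGG enrichment and Benjamini-Hochberg control at 0.05 complete the list.

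**Interpretation (Discussion).** The enrichment of differential metabolites "will specifically highlight altered host or microbial metabolic pathways". The authors want to go further than correlation and infer possible causal pathways, although they also call the work hypothesis-generating. The Discussion also names quercetin as a constituent of five of the seven CJG components, and curcumin as derived from *C. longa*.

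**The concern.** Untargeted metabolomics measures whatever is in the specimen, including what the participant swallowed. After baseline the arms differ by design in what they swallow, several grams at a time and three times a day. A plant compound or its breakdown product can therefore appear as a differential metabolite through ingestion alone. It would meet the selection rule, enter the KEGG enrichment, and be read as a change in host or microbial metabolism.

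Mechanism is one of the trial's stated aims. At stake is whether a pathway reported as altered says something about how CJG acts, or only that one arm took CJG and the other did not. Randomisation and blinding offer no protection, because the product is the randomised exposure.

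**Working it through.** **1. Can the design separate ingestion from response?**

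| Element | Where | Consequence |
|---|---|---|
| Chinese herbal medicines excluded for the preceding 3 months | 2.4 | Baseline samples are off product |
| Later samples at months 1, 2 and 3 of treatment | 2.7.4 | All later samples are on product |
| Herbal extract against mainly maltodextrin and colouring | 2.6 | Herb-derived compounds are supplied to one arm only |
| Alignment, de-noising, normalisation, supervised models, VIP and *p* filter, KEGG, FDR | 2.7.4 | No listed step tests whether a feature is in the product |
| Differential metabolites read as host or microbial pathways | Discussion | The reading assumes a separation that no listed step makes |

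Both available contrasts, CJG against placebo on treatment and CJG on treatment against its own baseline, mix response with presence of the product.

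**2. Number of participants available.** The article gives no sample size for the metabolomics, so I use the trial's own. Section 2.9 gives changes of 1.11 ± 2.12 mm and 0.19 ± 1.25 mm, two-sided α = 0.05, 90% power and 10% dropout. The difference is 1.11 − 0.19 = 0.92 mm. A noncentral *t* calculation needs 77 evaluable per group (power 90.2%), and 77 / 0.9 = 85.6, which rounds up to the stated 86. I take n = 77 per arm and assume all of them give samples.

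**3. Would the stated filters stop a product-derived feature?** The effect sizes and detection rates here are my assumptions; the document gives none. An α of 0.001 is an assumed stand-in for FDR control.

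For a feature differing by *d* standard deviations, power ≈ Φ(*d*√(n/2) − z), with z = 1.960 for α = 0.05 and 3.291 for α = 0.001, and √(77/2) = 6.205. For example, *d* = 0.5 at α = 0.05 gives Φ(3.102 − 1.960) = Φ(1.142) = 87%.

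| Assumed difference | Passes α = 0.05 | Passes α = 0.001 |
|---|---|---|
| 0.25 SD | 34% | 4% |
| 0.5 SD | 87% | 43% |
| 0.75 SD | 99.7% | 91% |
| 1.0 SD | >99.9% | 99.8% |

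For a compound detected in a share *p*₁ of the CJG arm and *p*₂ = 2% of the placebo arm, power ≈ Φ((p₁ − p₂ − z√(2p̄(1−p̄)/n)) / √((p₁(1−p₁) + p₂(1−p₂))/n)). With p₁ = 30%, p̄ = 0.16 and the two standard errors are 0.0591 and 0.0546. At α = 0.05 this is Φ((0.28 − 0.1158)/0.0546) = Φ(3.01) = 99.9%. At α = 0.001 it is Φ((0.28 − 0.1944)/0.0546) = Φ(1.57) = 94%. With p₁ = 10% the results are 55% and 11%.

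A clear product-derived difference therefore usually passes the *p*-value filter, while a weak one often does not. The VIP filter cannot be computed without data, but it ranks features by how well they separate the groups and does not ask where they come from.

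**4. Why FDR control does not answer this.** Benjamini-Hochberg limits the expected share of selected features with no true difference. A product-derived feature has a true difference, so it lies outside what the procedure controls.

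**The case against.** The strongest objection is that this is an argument from silence. The article gives metabolomics processing one short paragraph, and annotation or exclusion of exogenous compounds could sit in a laboratory procedure or the full protocol. That stands as far as it goes: the article does not say that product features will be kept, and a reader should not infer that they will not be removed. The point survives because the Discussion makes a positive attribution which the steps on the page do not support. The article also gives room to smaller ingested influences, such as yogurt and probiotics, expressly to protect these assays.

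Other objections stand in part:

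- **Saliva.** Doses follow meals, so a 2-hour fast will normally separate the sample from the last dose, and the mouth is rinsed. The concern is mainly with stool.
- **Carriers.** The excipient list for CJG is open-ended and the placebo is described only by its main ingredients. How far the carriers differ is not known.
- **Background.** Quercetin may also come from diet, so it need not be confined to the CJG arm.
- **Quantity.** Three 6 g packets for 90 days is 3 × 6 × 90 = 1,620 g, but that is gross granule mass including excipients. It says nothing about how many features differ.
- **Removal can overreach.** The Discussion gives the microbiota a role in how TCM acts, so microbial conversion products of herb compounds may belong to the hypothesised mechanism. Deleting all derivatives would discard them.
- **Status.** The outcome is exploratory and described as hypothesis-generating. Sampling on treatment is natural in a study of change under treatment and is not in itself a fault.

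**Conclusion.** The point holds in a limited form. As described, on-treatment sampling with no stated handling of product-derived features cannot tell ingested compounds from altered host or microbial metabolism, so the attribution in the Discussion is not supported as written.

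A reader might go further and infer that the product itself will be reported as mechanism, that its compounds will lead the VIP ranking, or that they will pass any threshold. The document supports none of these. It has no data on absorption, detectability, dietary background or mapping to KEGG. Under the assumptions above, a 0.5 SD difference passes α = 0.001 only 43% of the time. What can be said is that the stated rules do not prevent misattribution; its extent cannot be derived.

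The consequence is confined to the exploratory metabolomics, chiefly in stool. The primary, secondary and 16S analyses and the sample size are not directly affected. The conclusion assumes that no undisclosed filter exists; if one does, stating it and narrowing the Discussion's claim would settle the matter.

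**What to change.** In section 2.7.4, before KEGG enrichment:

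1. Flag features that are annotated constituents of CJG (quercetin and curcumin, for example) or that are found in reference injections of the CJG and placebo granules on the platform used for the specimens.
2. Report flagged features separately as exposure markers, and run the main enrichment without them.
3. Keep likely microbial conversion products of herb compounds as a separately labelled class, and give a sensitivity enrichment that includes them.
4. Record time since last dose at each saliva and stool sampling. This must be done prospectively.
5. In the Discussion, limit the attribution to host or microbial pathways to unflagged features.

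The platform must be named consistently first: section 2.7.4 says LC–MS, while the Abstract, Introduction and Discussion say GC–MS.

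The cost is two reference injections, one extra field at sampling, retained granules of both products, and a sensitivity run. The drawback is that some endogenous compounds which also occur in the granules drop out of the main enrichment. Visits, dosing and the primary analysis are unchanged.

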Traditional Chinese Medicine (TCM) presents potential clinical benefits for the “preventive treatment” (zhi wei bing) of pulmonary nodules and early-stage lung cancer. The prolonged surveillance period during follow-up observation provides an ideal opportunity for TCM intervention, which may contribute to the reduction of nodule volume, prevention of malignant transformation, and alleviation of clinical symptoms (11–13). Chuanjie Granules (CJG), a TCM compound granule formulation developed by our research team, is based on extensive clinical experience in the treatment of pulmonary nodules. This formulation consists of seven herbal components: *Vaccaria segetalis, Platycodon grandiflorus, Achyranthes bidentata, Citrus aurantium, Trichosanthes kirilowii, Curcuma longa,* and *Pumex*. The formulation has been submitted for a Chinese invention patent (application no. 202510241770.3). An initial investigation involving 91 patients indicated that CJG significantly decreased nodule size, with a total effective rate of 52.2% (*p* < 0.05) specifically concerning the reduction in diameter of pGGNs (14). Moreover, CJG was well-tolerated and proved effective in enhancing patient quality of life while mitigating symptoms of anxiety and depression. Nonetheless, the study’s findings were constrained by its single-center design, limited sample size, and absence of a placebo control.

To address this, we will conduct a high-quality, randomized, triple-blind, placebo-controlled, multicenter trial to assess the efficacy and safety of CJG. Additionally, we aim to explore its mechanism, hypothesizing its therapeutic effects may involve modulation of the host microbiota and consequent alterations in metabolite profiles. In pursuit of this objective, the study will incorporate 16S rRNA gene sequencing for the analysis of oral and gut microbiota, alongside untargeted metabolomic profiling of saliva and stool samples using gas chromatography–mass spectrometry (GC-MS).

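### Stool frozen at −20 °C is then carried on ice before −80 °C storage, so it can warm, partly thaw and refreeze before sequencing and metabolomics

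*Protocol article*

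**What the plan says.** Section 2.7.4 (Exploratory outcomes) sets one cold chain for each sample type.

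- **Saliva:** about 2–3 mL is collected in a sterile tube, "which will then be frozen on dry ice and stored at −80° C".
- **Stool:** "participants will collect approximately 5 g at home using sterile tools, avoiding air exposure and toilet water". The samples are first held at −20 °C and "later transferred on ice to a central lab for storage at" −80 °C.

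Both are collected at baseline and at months 1, 2 and 3. Both go to sequencing ("The V3-V4 regions of 16S rRNA will be amplified for high-throughput sequencing") and, according to the Introduction, to "untargeted metabolomic profiling of saliva and stool samples". The one check named ahead of the sequencing work is a general one: "After assessing sample quality, total genomic DNA from microbial communities will be extracted".

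**The concern.** The paragraph names dry ice for saliva and ice for stool within a few lines, so the two terms are best read as different things. Plain ice is about 20 °C warmer than the −20 °C at which the stool was held, and slightly above the temperature at which stool water is likely to melt. Transfer on ice is therefore a warming step, and the −80 °C step may be a second freeze.

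While part of the water is liquid, bacteria and enzymes can change the small molecules that untargeted metabolomics measures. The 16S profile is probably less exposed. How far this goes depends on how long each sample travels, so it adds variation that has nothing to do with CJG.

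This bears on the trial's own aims. Section 2.6 asks participants to avoid probiotics and yogurt in order to protect these same analyses. The Discussion says that unstable microbial findings limited the team's previous gut-microbiota study of CJG.

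**Working it through.** There is no figure in the document to reproduce, so the check has two parts.

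**1. The printed temperature path**

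| Sample | First step | Transport | Final storage |
|---|---|---|---|
| Saliva | dry ice | no separate step named | −80 °C |
| Stool | −20 °C | ice, about 0 °C | −80 °C |

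Only stool has a printed step that is warmer than the one before it.

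**2. How fast a 5 g sample would warm**

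The 5 g and the −20 °C start come from section 2.7.4. The rest are assumptions:
- heat capacity c = 2 J/g/K
- latent heat λ = 250 J per g of sample
- heat transfer 20 W/m²/K over 15 cm², so hA = 20 × 0.0015 = 0.03 W/K
- surroundings at 0 °C
- osmolality 0.2 to 0.4 Osm/kg

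The freezing point lies θf = 1.86 × osmolality degrees below zero: 0.37 °C at 0.2 Osm/kg and 0.74 °C at 0.4 Osm/kg. At θ degrees below zero, the unfrozen share of the water is about θf/θ:
- −20 °C: 2–4%
- −5 °C: 7–15%
- −1 °C: 37–74%

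Ice melts progressively during warming, so latent heat has to be included. Integrating the heat balance from −20 °C gives

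t(θ) = (m/hA) × [c·ln(20/θ) + (λθf/2)(1/θ² − 1/20²)], with m/hA = 5/0.03 = 166.7.

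The factor λθf/2 is 46.5 at the lower osmolality and 93 at the higher.

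- **To −5 °C:** 166.7 × (2.77 + 46.5 × 0.0375) = 753 s, about 13 min. At the higher osmolality, 166.7 × (2.77 + 93 × 0.0375) = 1,043 s, about 17 min.
- **To −1 °C:** 166.7 × (5.99 + 46.5 × 0.9975) ≈ 8,730 s, about 2.4 h. At the higher osmolality, 166.7 × (5.99 + 93 × 0.9975) ≈ 16,460 s, about 4.6 h.
- **To full thaw (θ = θf):** about 16 h at the lower osmolality and 8 h at the higher.

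All times scale as 1/hA: half the heat transfer doubles them. If the box sits at 4 °C rather than 0 °C, full thaw takes about 2 to 2.4 h. Under these inputs, partial softening needs only an ordinary journey. Full thaw needs a long one or a box warmer than ice.

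**3. How many samples**

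172 participants × 4 visits = 688 at most. Section 2.9 expects 10% dropout. If those participants gave no stool at all, the count would be about 688 × 0.9 ≈ 619.

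**The case against.** The strongest case against is that nothing here is a contradiction. Two sample types may have two cold chains, stool is collected at home, and no direct saliva–stool comparison is specified. Harm depends on transit time, container and amount of ice, which an article normally leaves to a laboratory manual. Section 2.12 mentions standard operating procedures, and sample quality is to be assessed. The outcomes are exploratory, and the Discussion presents the bioinformatic work as generating hypotheses.

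Much of this stands. The missing transit limit is not a finding in itself, and the difference from saliva matters only because it shows how to read the word ice. What does not fall away is that the article prints a specific transport condition, and that condition is the weak step. If dry ice was meant, the sentence still needs correcting.

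A reader might also infer more than the document supports:
- **That stool is near its melting point within half an hour.** That follows only if latent heat is ignored. With it, only about −5 °C is reached in that time.
- **That transit differs by centre or visit and would mimic a centre or time effect.** The document gives no transit times and states one procedure for all.
- **That samples sit in home freezers.** Collection is at home, but the place of the −20 °C storage is not stated.
- **That stool is the main evidence for the mechanism.** Saliva has equal standing in the Introduction and in section 2.7.4.
- **That the comparison of arms is biased.** Handling is the same in both arms of a triple-blind trial.

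**Conclusion.** The point holds as a minor, avoidable weakness. The printed stool path allows warming and partial thaw, followed by refreezing, before sequencing and metabolomics. It does not show that any sample will thaw fully. The conclusion rests on reading the stool transport as plain ice, and the timings rest on the assumed heat transfer, latent heat and osmolality.

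The expected consequence is added noise, and so less ability to detect true changes in exploratory stool measures. Diameter, sample size and safety analyses are not affected.

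**What to change.** In section 2.7.4, replace the stool transport wording so that stool travels frozen without thaw, either on dry ice as already named for saliva or in a validated frozen transport box. Have the central laboratory record on receipt, blind to arm, whether each stool sample arrived thawed. Repeat the stool metabolomics without the flagged samples as a sensitivity analysis.

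The cost is modest: dry ice or transport boxes for stool, and one extra field at receipt. Section 2.13 gives a planned start of recruitment, so the change is best made before the first stool is shipped, because a thawed sample cannot be restored. If recruitment has begun, the change and the flag can still apply to later samples, with the date of the change recorded.

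### As written, the MaAsLin analysis relates genus abundance to time only and cannot by itself attribute microbiome change to CJG; the metabolite threshold and the platform are also stated inconsistently

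*Protocol article*

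**What the plan says.** All three points concern section 2.7.4 (Exploratory outcomes) of the protocol article.

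- **Microbiome.** Sampling is described as follows: "Paired saliva and feces samples will be collected at baseline, mid-term (months 1 and 2), and end (month 3) of CJG treatment". The analysis list includes alpha and beta diversity, "genus-level species differentiation via Linear discriminant analysis Effect Size (LEfSe"), and "examining the relationship between microbial genus abundance and time using multivariate linear association (MaAsLin"). No arm term is named for MaAsLin, and the classes that LEfSe compares are not named.
- **Metabolites.** PCA, PLS-DA and OPLS-DA are listed, and they "identified differential metabolites (VIP > 1 and *p* < 0.05"). KEGG enrichment comes next. The sentence after that reads "The Benjamini-Hochberg method was used to calculate the false-discovery rate (FDR) for multiple comparisons, with significance set at" an FDR-adjusted p below 0.05. The tests it covers are not named.
- **Platform.** Section 2.7.4 says "the supernatant was analyzed by LC–MS". The Introduction says "untargeted metabolomic profiling of saliva and stool samples using gas chromatography–mass spectrometry (GC-MS"), and the Abstract and the Discussion also name GC-MS.

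The Discussion hopes to go past association and infer causal pathways of CJG, and in the same paragraph calls the work hypothesis-generating.

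**The concern.** A change over time within participants is not a treatment effect. Both arms receive health education on diet, smoking, alcohol and exercise, and in both arms "participants will be advised to abstain from consuming probiotics" throughout treatment (section 2.6). Genus abundance could therefore move over three months without any action of CJG. A time-only relation would count that shared movement as signal, and could equally hide a real CJG effect that runs against it. The trial has a randomised placebo arm that separates the two, and the stated relation does not use it.

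The other two points are separate. If differential metabolites enter KEGG enrichment at p < 0.05, the pathway list rests on a looser rule than the FDR threshold given two sentences later. And a reader cannot tell which instrument will produce the metabolite data. At stake is what may be said about mechanism, not the efficacy or safety conclusions.

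**Working it through.** **The plan's own figure.** The article gives no size or power figure for the omics data. The only such figure is 86 per group for the primary outcome (section 2.9: 1.11 ± 2.12 mm against 0.19 ± 1.25 mm, two-sided alpha 0.05, power 0.90, 10% dropout). A noncentral t calculation needs 77 per arm, and 77/0.9 = 85.6, rounded up to 86. It reproduces. It does not bear on this point, except that 77 completers per arm is used below.

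**Step 1: the two longitudinal models side by side.** For the primary outcome, section 2.14 names group, time point and their interaction as fixed effects, with a random subject intercept. For genus abundance, section 2.7.4 names time. The article thus gives model terms in both places, and only the first contains the arm comparison.

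**Step 2: what a time-only relation estimates.** Let a participant's change in a genus, in SD units, have mean δ + τ on CJG and δ on placebo, where δ is drift shared by both arms and τ is the CJG effect. With 1:1 allocation:

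- time-only, pooled over arms: estimates δ + τ/2
- difference between arms in change: estimates τ

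Only the second is free of δ.

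**Step 3: illustration.** The values of δ and τ are assumed, because the article gives none for the omics data. There were 4,000 simulated trials with 77 per arm, change SD 1 and two-sided 0.05. One change per participant was tested, as a simplification of the four-visit data.

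| Shared drift δ | CJG effect τ | Time-only rejects | Between-arm rejects |
|---|---|---|---|
| 0 | 0 | 5.1% | 4.9% |
| 0.2 | 0 | 69.5% | 4.6% |
| 0.3 | 0 | 96.2% | 5.2% |
| −0.25 | 0.5 | 4.2% | 86.4% |

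Hand check of rows 2 and 3, with 154 participants pooled: 0.2 × √154 = 2.48 and Φ(2.48 − 1.96) = Φ(0.52) ≈ 0.70; 0.3 × √154 = 3.72 and Φ(1.76) ≈ 0.96. In row 4 the time-only mean is −0.25 + 0.5/2 = 0, so a real effect is missed.

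If the time relation were fitted in the CJG arm alone (n = 77), the problem would remain. With no CJG effect, 0.2 × √77 = 1.755 gives Φ(−0.205) ≈ 0.42, and 0.3 × √77 = 2.632 gives Φ(0.672) ≈ 0.75.

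**Step 4: the two metabolite thresholds.** The FDR sentence can be read in at least two ways. If it covers the metabolite tests, a plain p < 0.05 is not the operative rule and should not stand as the definition of a differential metabolite. If it covers only the pathway tests, the metabolites entering KEGG enrichment are selected without adjustment. The text does not decide between these.

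**Step 5: platform.** LC-MS appears in section 2.7.4; GC-MS appears in the Abstract, Introduction and Discussion. The Introduction and section 2.7.4 both describe saliva and stool or feces, so the difference cannot be explained by sample type.

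**The case against.** The strongest reply is that half a sentence on one method does not define the whole mechanism analysis. LEfSe, PLS-DA and OPLS-DA compare classes, and in a placebo-controlled trial those classes may well be the arms. The MaAsLin sentence names a relationship of interest rather than a full formula, and an analysis plan that is not shown may give the terms. This stands to a large extent. A reader might infer that the mechanism analysis as a whole cannot attribute anything to CJG; the document does not support that. What remains is that the one longitudinal relation stated is with time, while the same article names the arm interaction for its primary outcome and states a causal aim for the omics work.

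Other stronger readings also fail:

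- **Samples from the CJG arm only.** The wording about CJG treatment invites this reading. However, section 2.6 places the probiotic restriction on all eligible participants expressly to protect the microbiome and metabolomics analyses, and participants and investigators are blinded (section 2.11). Both imply sampling in both arms.
- **Probiotic withdrawal as the source of drift.** Abstention starts a week before enrolment (section 2.6), and recent yogurt or probiotic use is an exclusion (section 2.4), so baseline already follows a week without them. Continued abstention and the lifestyle advice could still produce a shared trend, but its size is unknown.
- **Pathway analysis filled with false positives.** A count of 0.05 times the number of metabolites would need a metabolite number that the article does not give, and it would ignore both the VIP filter and the FDR step. Only the lack of reconciliation is shown.
- **Platform clash as an attribution problem.** It is a contradiction about how an outcome is measured and has no bearing on attribution.

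Finally, the outcomes are labelled exploratory, which limits the consequence.

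**Conclusion.** The point holds in a limited form. Followed as written, the MaAsLin analysis cannot by itself attribute microbiome change to CJG, because it relates abundance to time and leaves the randomised contrast unused. Two inconsistencies stand beside it: two metabolite thresholds with no stated link, and LC-MS against GC-MS. An unseen analysis plan could supply model terms and the scope of the FDR, but it cannot make both platform statements true.

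The rejection rates of about 70% to 96% against about 5% show the direction of the problem under assumed drifts of 0.2 to 0.3 SD, a change SD of 1 and 77 per arm. They are not estimates for this trial. The effect is confined to the mechanism conclusions; the primary model already contains group, time and their interaction. This is a worthwhile improvement, not a threat to the trial's main result.

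**What to change.** 1. Fit MaAsLin with group, time and group-by-time as fixed effects and participant as random effect, and base any statement about CJG on group-by-time. This can be run on the coded A/B labels available after the first unblinding. In the same edit, say whether the LEfSe and (O)PLS-DA classes are arms or visits, and that both arms are sampled.
2. Apply the FDR-adjusted p < 0.05 to a between-arm metabolite comparison before KEGG enrichment, or label VIP > 1 with p < 0.05 as screening only. Name the tests that the FDR covers.
3. State the one metabolomics platform to be used throughout, and align the extraction text with it.
4. Soften the causal wording in the Discussion unless the arm contrast is specified.

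The cost is a few sentences and a different model formula, with no extra participants or visits. FDR selection will leave fewer candidate metabolites. The changes should be fixed before the omics data are analysed.
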